**Primary outcome**					
	Number of participants with a written asthma action plan	Pre and post-study surveys	X		X

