#### Primary Analysis

Differences in proportions of participants visiting their GP to obtain/update their written asthma action plan during the study will be compared between control and PCHMS groups. All intervention recipients who had the opportunity to use the PCHMS but did not do so will be included in the primary analysis (intention-to-treat principle with Last Observation Carried Forward (LOCF) imputation procedure for missing values [35,36]). Differences in participant proportions between control and PCHMS groups will be analyzed using χ^2^test or Student’s *t*-test. Proportions will be reported with 95% confidence intervals. Adjustments for baseline characteristics and possible confounders, such as age and other demographics [2,3], smoking status [3], and asthma severity [2], will be made through the use of sequential logistic regression [37]. All baseline characteristics, and factors that may affect the written asthma action plan possession rate collected at post study (eg, past possession of an asthma action plan) will be entered at step 1 of the regression; and group allocation (PCHMS vs. control) will be entered at step 2.

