### Study Procedure

Table 3 below summarizes participant procedures in the study. The duration of the study is expected to be 12 months.

Email will be the primary channel to communicate with participants for study information and reminders about survey completion. From the time participants are recruited until study completion, all participants (control and intervention) will receive an email each month to complete a 5-minute survey about their health in the past month. At study completion, all participants will receive an email asking them to complete a post-study survey. In order to ensure the completeness of data collection, there will be 2 follow-up emails sent 5 days apart from each other to remind those who have not completed each survey.

**Table 2 table2:** Surveys used in the study.

Survey	Purpose
Screening survey	Eliciting participants’ eligibility criteria.
Pre-trial survey	To obtain participants’ demographics and experiences of asthma management at study enrolment.
Monthly follow-up questions	To obtain participants’ self-reported symptoms of asthma (ie, asthma control and exacerbation), impact on work and study due to asthma symptoms, and competing demands and health throughout the study.
Post-trial survey (12 months after the beginning of the study)	To obtain participants’ state of asthma control and asthma management. For those who receive the PCHMS version of *Healthy.me*, their perceived usefulness of *Healthy.me* will also be assessed.

**Table 3 table3:** Stages of study procedure.

Stage of study	Procedure

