### Concluding Remarks

Most of the features used in the study have been recently tested in a *Healthy.me* trial on help-seeking behaviors for physical and emotional well-being in a university student population [25]. The results of that study have shown that some bundles of features could lead to behavioral changes in university health service utilization and reported help-seeking for physical and/or emotional concerns. These results were consistent with theoretical expectations of behavioral changes generated from the use of features in *Healthy.me*. Particularly, the Health Belief Model (HBM) provides insights on how information may be transformed into action when informational cues in the environment are linked to action [41]. In the present study, we expect that the use of the online appointment booking service will be significantly associated with visits to health professionals, and consequently with a high rate in obtaining an asthma action plan. Another lever of behavioral change in accord with the principle of self-monitoring, may be operate thanks to features which encourage self-refection and self-awareness, such as the Personal Health Record, the Pillbox, the Diary, and the Poll [42]. In addition, the social and interactive features used in *Healthy.me* (Forums, Poll, Message) should play an important role in minimizing attrition and in promoting utilization of the platform amongst participants during the 12 months of the study [9].

Our design of the present randomized controlled trial (RCT) focuses on the comparison of outcomes that unequivocally reflect a change in consumer behavior, and takes into account the complexity of intervention. Results of this study will offer new insights about the utility of a Personally Controlled Health Management System (PCHMS) for consumer engagement with e-health services and self-management. Our findings will provide specific answers to whether using a Web-based PHCMS, containing information and self-management tools that facilitate consumers to engage with health services, will improve the uptake of preventive asthma management actions such as the possession and use of a written asthma action plan.

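### As worded, the adjusted primary regression admits covariates from the 12-month survey; conditioning on any that the intervention can change would stop the group coefficient estimating the randomised effect

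*Protocol article*

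**What the plan says.** All of this is in the Protocol article.

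- Primary Analysis specifies an unadjusted comparison first: "Differences in participant proportions between control and PCHMS groups will be analyzed using χ^2^test or Student’s *t*-test".
- The same paragraph adds a sequential logistic regression to adjust for baseline characteristics and possible confounders. Its covariates are the full set of baseline characteristics together with "factors that may affect the written asthma action plan possession rate collected at post study (eg, past possession of an asthma action plan". These "will be entered at step 1 of the regression; and group allocation (PCHMS vs. control) will be entered at step 2".
- Study Procedure, Table 2, times the last survey: "Post-trial survey (12 months after the beginning of the study". Its stated purpose is "To obtain participants’ state of asthma control and asthma management".
- Table 1 lists planned and unplanned healthcare visits as secondary outcomes taken from the post-study survey. It lists the primary outcome as measured by "Pre and post-study surveys", so plan possession is also recorded at baseline.
- Concluding Remarks gives the expected mechanism: "we expect that the use of the online appointment booking service will be significantly associated with visits to health professionals". It goes on to say that more plans should be obtained as a consequence.

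**The concern.** A covariate measured after randomisation may itself be a result of treatment. If the model holds such a variable fixed, it compares participants who ended up alike on a consequence of allocation. The part of the effect that runs through that variable is then taken out of the group coefficient.

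Here the regression sits under the primary analysis, and the clause on post-study factors is open-ended. GP visits fit it: they affect whether a plan is obtained, and they are collected in the post-study survey. They are also the route by which the authors expect the intervention to work. An adjusted result built this way could be weaker than the unadjusted test for no reason other than the choice of covariates.

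**Working it through.** **Step 1. What the wording admits.** The covariate list opens "All baseline characteristics, and factors that may affect the written asthma action plan possession rate". Every baseline characteristic is already in the first part, so the factors after the conjunction are a further set, and the text goes on to say they are collected at post study. Nothing limits them to attributes fixed before randomisation. The single example is given as an example and does not close the list.

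**Step 2. The plan's own figures.** Sample Size gives 14.4% (control) and 29.4% (intervention), 150 per arm and about 25% dropout.

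- Size per arm, pooled variance, two-sided 5%, 80% power: [1.960 × √(2 × 0.219 × 0.781) + 0.842 × √(0.144 × 0.856 + 0.294 × 0.706)]² / 0.15² = 118.1, so 119. Then 119 × 1.25 = 148.75, so 149 per arm and 298 in total, close to the stated 300. The present point does not depend on this.
- Unadjusted odds ratio: (0.294/0.706) / (0.144/0.856) = 0.4164/0.1682 = 2.48.
- Analysed per arm: 150 × 0.75 = 112.5. At 112 to 113 per arm the unadjusted comparison has about 78% power.

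The document gives no figure for the adjusted effect, so steps 3 and 4 are illustrations under assumptions.

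**Step 3. A post-study factor on the causal path.** Assume the factor is a planned GP visit during the study, with rate m0 in control and m1 in intervention, carrying a share k of the 15-point effect. The total rates stay at 14.4% and 29.4%.

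- Risk difference for a visit: s = k × 0.15 / (m1 − m0)
- Control rate without a visit: q0 = 0.144 − s × m0
- Direct effect: d = (1 − k) × 0.15

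Example with m0 = 20%, m1 = 50%, k = 50%: s = 0.075/0.30 = 0.25, q0 = 0.144 − 0.05 = 0.094, d = 0.075. The rates without and with a visit are 9.4% and 34.4% in control, and 16.9% and 41.9% in intervention. Check: 0.8 × 0.094 + 0.2 × 0.344 = 0.144, and 0.5 × 0.169 + 0.5 × 0.419 = 0.294. The within-stratum odds ratios are 1.96 and 1.38, and the fitted common value is 1.65.

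Adjusted odds ratio for group from the large-sample logistic fit, with approximate Wald power at 112.5 per arm in brackets:

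| Visit rate, control / intervention | k = 0% | 25% | 50% | 75% | 100% |
|---|---|---|---|---|---|
| 30% / 50% | 2.48 (75%) | 2.05 (53%) | 1.76 (32%) | – | – |
| 30% / 60% | 2.48 (73%) | 2.01 (50%) | 1.65 (28%) | 1.33 (11%) | – |
| 20% / 50% | 2.48 (72%) | 2.02 (50%) | 1.65 (28%) | 1.33 (11%) | 1.00 |

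A dash marks a combination that would need a negative rate.

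**Step 4. The article's own example.** Assume true past possession of 14.4% in both arms, an outcome rate 1.5 times the arm's overall rate among those with past possession, and a fraction f of the other participants who obtain a plan in the study reporting it at 12 months as past possession. The fraction f is the same in both arms.

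| f | Adjusted odds ratio | Power |
|---|---|---|
| 0% | 2.50 | 77% |
| 25% | 2.55 | 75% |
| 50% | 2.61 | 70% |
| 75% | 2.69 | 62% |

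The odds ratio does not fall. Power does.

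**Step 5. Order of entry.** The final model contains the covariates and group whichever block goes in first, so the final group coefficient is the same. Only the presence of the post-study variable matters.

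**The case against.** The best case for the plan is that the authors meant pre-study attributes. The words on post-study collection can be attached to the possession rate, which is itself measured in that survey, and not to the factors. The only example is nominally a pre-study attribute. The preceding sentence speaks of baseline characteristics and confounders, and Limitations treats prior plan history as a baseline variable. No mediator is named as a covariate: visits appear as secondary outcomes, and the mechanism is stated only in the concluding discussion. The unadjusted comparison comes first and matches the sample-size basis.

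Much of this stands. The intention may well have been harmless, and the sizes in step 3 belong to an assumed covariate. But the alternative parsing sets no timing limit on the factors at all, so it does not exclude post-randomisation variables. Nor is this a detail left to a fuller document: the article states a covariate rule, and the rule as stated permits the wrong variables.

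A reader might go further in three ways that the document does not support:

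- That these covariates turn the analysis into one of completers only. Participants who do not return the post-study survey lack the 12-month outcome from that same survey anyway, and the paragraph states LOCF for missing values. Whether LOCF is suitable is a separate question.
- That the model is overfitted. The number of baseline covariates is not given, and limits based on events per variable are rules of thumb.
- That entering the factors before group is what causes the loss. Step 5 shows that it is not.

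**Conclusion.** The point holds for the adjusted regression. Its wording allows conditioning on 12-month variables, and any that the intervention can change would stop the group coefficient from estimating the randomised effect.

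The size is not fixed by the document. With an assumed visit mediator carrying 25% to 75% of the effect, the odds ratio falls from 2.48 to between about 2.0 and 1.3, and power from 72–75% to between about 53% and 11%. With past possession, under equal misreporting in the two arms, there is no attenuation, and power falls from about 77% to between 75% and 62%. Misreporting that differs by arm is outside that calculation.

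It would be wrong to infer that the primary result as a whole is biased: the chi-square comparison uses no covariates and is untouched. It would also be wrong to read the article as having chosen to adjust for GP visits. It leaves the door open to them and does not name them.

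**What to change.** In Primary Analysis, delete the clause that admits factors collected at post study and limit the adjustment set to variables measured before allocation:

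- gender and asthma severity, the stratification factors under Randomization;
- past plan possession, taken from the pre-study survey, which participants complete before their group is revealed to them;
- age and smoking status, which the article already names as baseline variables.

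Report any model that includes post-study factors, such as visits or booking use, separately and label it an exploratory or mediation analysis.

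The cost is one sentence in the analysis plan. Plan possession is already measured at baseline and the other variables are ones the article already intends to use, so no new data item is called for. The change should be made before group allocation is unblinded, so that the covariate set cannot be chosen with results in view.

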#### Secondary and Ancillary Analysis

Differences in proportions of participants between different groups (eg, control vs. PCHMS) will be examined using χ^2^test based on data collected from pre-, monthly, and post-intervention questionnaires, for each of the following activities experienced at least once during the study: (1) visited a GP (or a healthcare professional) for an unplanned asthma visit; (2) used medications or remedy; and (3) experienced performance impairment. Differences in average number of days of absence per participant and differences in score distributions from questionnaires will be compared between control and PCHMS groups using Student’s *t*-test or non-parametric statistics. Reasons for receiving (or not receiving) written asthma action plan will be reported using descriptive statistics. Attrition rate for the use of *Healthy.me* will be assessed with system logs. Technology acceptance of *Healthy.me* will be measured via the “Scales for Perceived Usefulness and Perceived Ease of Use” [30,38]. Participants’ satisfaction and utilization of Healthy.me will be reported. Cost effectiveness of health service utilization [39] (upon availability and feasibility) will also be considered as well as economic costs from days lost from work/school. If any post-hoc comparison would need to be performed between unplanned groups of participants, a Holm’s sequential Bonferroni procedure [40] will be used in order to control a familywise error rate *FWER* inferior or equal to level α = .05.

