### Sample Size

A conservative estimate of at least 300 participants with 150 in each arm is needed to detect a 15% point difference in possession rate of a written asthma action plan between the control group (14.4%) and the intervention group (29.4%). This estimate is calculated at 5% level of significance, 80% power (2-sided test), with an anticipated participant dropout rate approximately 25%.

The effect size estimate is based on previous studies using *Healthy.me* assessing the efficacy of Internet-based interventions on the uptake of preventative health actions [23], and on studies with interventions promoting the use of personal asthma action plans [13]. The base rate is the percentage of adults (ie, 15 years and over) with current asthma in Australia and possessing a written asthma action plan, reported in the Australia Centre for Asthma Monitoring analysis of the Australian Bureau of Statistics National Health Survey 2007-2008, and cited in the Australia Centre for Asthma Monitoring 2011 report [2].

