### Analysis Plan

Statistical significance is defined as a *P*-value of less than .05 (determined using a two-tailed test). Data will be collected by online survey software KeySurvey [33] and analyzed using IBM SPSS Statistics 19 [34].

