## Discussion

### Limitations

There are several potential limitations in this study. Firstly, the number of participants meeting inclusion criteria at study completion might be low because the study will focus recruitment only in Australia. The other inclusion criteria such as age, Internet access, and English speaking skills, might be also restrictive for recruiting participant in the targeted population.

Secondly, there is a possible high attrition rates*.* The study’s outcomes will rely on data from participants’ self-reports. Due to the long duration of the study, over 12 months, it is possible to observe a high rate of attrition from participants and thus, a significant loss of data. To limit this, all participants will be actively requested to complete questionnaires by receiving monthly reminders via emails. Furthermore, the questionnaires used on a monthly-basis will be easy and convenient complete (short questionnaires with an online completion using multiple-choice questions).

Thirdly, there may not be representative of consumers with asthma. The study may be more appealing to younger participants who are interested or literate in computers, the Internet, or asthma self-management topics. These participants may be more enthusiastic about health and the Internet than the general asthma population.

Fourthly, as this is a pragmatic trial of a multifaceted intervention in a complex environment, it is possible that baseline variables associated with participants might also influence the outcome. For example, having a prior history of obtaining a written asthma action plan may predict future planned visits to GP, independent of any additional intervention. We will identify potential baseline variables that might influence outcomes, including age and smoking status, and test for unequal variance in the distribution of these variables in the intervention and control populations.

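### The ever/never secondary outcomes, and days of absence if summed, have no denominator for monthly surveys returned, so unequal survey return between arms would create a difference with no true effect

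*Protocol article*

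**What the plan says.** Secondary and Ancillary Analysis lists three binary items: an unplanned asthma visit, use of medication or a remedy, and performance impairment. They are tested by chi-square on data pooled from the pre-study, monthly and post-study questionnaires, "for each of the following activities experienced at least once during the study". The same section compares "Differences in average number of days of absence per participant" by t-test or a non-parametric method. No term for months observed or surveys returned appears in either comparison.

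Study Procedure sends every participant one survey a month, with a one-month recall, and two reminder emails to non-completers, in both arms alike. Table 1 collects days lost from work or school monthly only. It takes unplanned visits from the post-study survey at completion, which does not match the pooled sources in the analysis section.

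On retention, Limitations says that "it is possible to observe a high rate of attrition from participants and thus, a significant loss of data". Concluding Remarks says that the social and interactive features, which controls do not have, "should play an important role in minimizing attrition and in promoting utilization of the platform amongst participants". Sample Size allows for one overall dropout of about 25%, with no figure by arm. Last observation carried forward is named under Primary Analysis only.

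**The concern.** A month with no returned survey cannot contribute an event or a day lost through the monthly channel. For days lost, Table 1 lists no other channel. An ever/never proportion therefore measures two things at once: how often the event happens, and for how many months the participant was observed. If observation time differs between arms, the comparison mixes a retention effect with an asthma effect.

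A difference is plausible here. The article itself expects attrition and names intervention-only features as a means of reducing it. If those features also keep people answering surveys, the distortion runs against Healthy.me and could hide a modest benefit on impairment and absence. Those outcomes bear on the second hypothesis and on the planned costing of lost days. Restricting the analysis to full responders would not solve this, because it replaces unequal observation with selection.

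**Working it through.** **The plan's own figure.** The only reproducible figure is the sample size, and this point does not dispute it. Two proportions of 14.4% and 29.4%, two-sided 5%, 80% power: 119 per arm. 119 × 1.25 = 148.75, so 149 per arm, or 298 in total, close to the stated 300. Only the arm size is carried forward ("at least 300 participants with 150 in each arm").

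**Inputs from the article.** 150 per arm; two-sided 5% (Analysis Plan); up to about 12 monthly surveys; overall dropout about 25%.

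**Assumed inputs, not in the article.** Monthly event risk q from 2% to 20%, the same in both arms and independent between months. Dropout of 20% (intervention) v 30% (control), which straddles the planned 25%, and a wider 15% v 35%. A participant who drops out returns k surveys, with k uniform on 0 to 11 (mean 5.5). Everyone stays in the denominator, and an unreturned month counts as no event.

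**Formulas.**
- P(ever | k surveys) = 1 − (1 − q)^k
- Arm proportion = (1 − d) × P(ever | 12) + d × mean of P(ever | k) over k = 0 to 11
- Mean surveys = 12(1 − d) + 5.5d
- Expected summed days = mean surveys × mean days per month

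**Worked case, q = 5%.** P(ever | 12) = 1 − 0.95^12 = 46.0%. The mean over k = 0 to 11 is 23.4%.
- Intervention: 0.80 × 46.0 + 0.20 × 23.4 = 41.4%
- Control: 0.70 × 46.0 + 0.30 × 23.4 = 39.2%

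**Results with no true effect** (rejection probability by normal approximation to the chi-square):

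| Monthly risk | 20% v 30% dropout: ever-proportion | Gap (points) | Type I error | 15% v 35% dropout: gap (points) | Type I error |
|---|---|---|---|---|---|
| 2% | 19.3% v 18.2% | 1.1 | 5.7% | 2.2 | 7.9% |
| 5% | 41.4% v 39.2% | 2.3 | 6.8% | 4.5 | 12.5% |
| 10% | 65.4% v 62.3% | 3.2 | 8.8% | 6.3 | 20.6% |
| 20% | 86.7% v 83.5% | 3.2 | 12.1% | 6.4 | 34.2% |

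**Summed days of absence.**
- 20% v 30%: mean surveys 12 × 0.80 + 5.5 × 0.20 = 10.70 v 12 × 0.70 + 5.5 × 0.30 = 10.05. The ratio is 1.065.
- 15% v 35%: 11.025 / 9.725 = 1.134.

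**Bounds.**
- Equal dropout of 25% in both arms: gap 0, type I error 5%, days ratio 1.00.
- Extreme case, 12 v 9 surveys for everyone: at 5% monthly risk the gap is 46.0% v 37.0%, and days are 33% higher (12/9). A true 20% reduction in monthly risk would then appear as 38.7% v 37.0%, and the days ratio as 0.80 × 12/9 = 1.07.
- Near-universal item, 50% per month, again 12 v 9 surveys: 100.0% v 99.8%, so almost nothing shows.
- Variation between people: a beta-binomial simulation at 15% monthly risk, within-person correlation 0.1 and about 20% v 30% dropout gives 66.0% v 63.0%, 8.2% rejection and 7% more days. Independence between months is therefore not what drives the result.

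**Per-month analysis.** With equal monthly risk, a rate per returned month has a true ratio of 1.00 whatever number of surveys each arm returns, provided dropout is unrelated to asthma state.

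**The case against.** The strongest objection is that unequal survey return is an inference. Concluding Remarks couples attrition with platform use, and the analysis section measures attrition of Healthy.me use from system logs. Survey return runs through a separate system, with the same emails and reminders in both arms. Controls are promised Healthy.me after 12 months, which may give them a reason to stay. This stands: neither the size nor the direction of a retention difference is documented. A reader might infer that the Healthy.me arm will look sicker. The article supports only the conditional statement.

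The scope is also narrower than the list of items suggests. Medication use may be close to universal and so show almost no effect. Unplanned visits are affected by the count of monthly surveys only if the pooled sources apply and not Table 1. The post-study questionnaire could recover some impairment, although the article does not say that it asks about it. That days are summed is the natural reading of a mean per participant, but not the article's wording.

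A reader might also infer that an imbalance would go unseen, because system logs exist for one arm only. That does not follow. Non-completers of every survey have to be identified for reminders, and allocation is coded in the survey tool, so return by arm is available.

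Finally, offsets and missing-data rules for secondary outcomes are often left to a fuller document, and their absence from an article is no fault. But the article does fix the summary measure and the test, and followed as written these can mislead.

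**Conclusion.** The point holds in conditional form. As specified, the ever/never comparison, chiefly for performance impairment, rises with the number of monthly surveys returned, and so does absence if days are summed. If return differs by arm, the better-retained arm shows more events without any true effect.

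For a 10-point dropout gap around the planned 25%, the distortion is modest: about 1 to 3 points, type I error about 6% to 12%, and 6.5% more days. It grows with the gap and vanishes with equal retention. All of this rests on assumed monthly risks and retention, and on dropout being unrelated to asthma state. If dropout is related to asthma state, the net bias could go either way.

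The primary outcome comes from the pre-study and post-study surveys and is untouched by this mechanism. The change is worth making because it is cheap, not because harm is certain.

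**What to change.** 1. Analyse returned person-months. For monthly yes/no items, use a mixed-effects logistic model, or GEE weighted for dropout (ordinary unweighted GEE generally needs data missing completely at random). For days of absence, use negative binomial regression of days over returned months, with the log of months covered as offset.
2. Report the number and proportion of surveys returned by month and arm. Keep Healthy.me log attrition as a separate measure of platform use.
3. Add a sensitivity analysis for dropout related to asthma state. A denominator alone does not repair that.
4. Reconcile the source of unplanned visits between Table 1 (post-study survey) and Secondary and Ancillary Analysis (pooled questionnaires), and state whether days of absence are summed or averaged over returned months.

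Leave the monthly recall wording unchanged. Asking about the time since the last completed survey would recover nothing from people who never return, and it would mix recall windows while recruitment is under way.

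The cost is analysis-plan wording and one extra table. Effects become per month instead of ever during the study, and unreturned months are assumed missing at random. The offset model assumes more: that the rate in unreturned months matches the rate in returned ones.

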**Results:**

The primary outcome measure is possession of or revision of an asthma action plan during the study. Secondary outcome measures include: (1) adherence to the asthma action plan, (2) rate of planned and unplanned visits to healthcare providers for asthma issues, (3) usage patterns of Healthy.me and attrition rates, (4) asthma control and asthma exacerbation scores, and (5) impact of asthma on life and competing demands, and days lost from work.

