#### Intervention Group and Exposure

The period of access to *Healthy.me* will vary depending on the date of participant registration (from 9 to 12 months). During the study *Healthy.me* will provide participants in the intervention group with information and forward email reminders about asthma, indications for managing their asthma or other medical concerns, should they wish to use that service.

The intervention will not modify in any way the standard procedures of healthcare provision by GP clinics.

A pilot study has been conducted with 9 adults including 3 participants with asthma. Issues on system usability, journey content, surveys, study protocol, and advertisement material have been resolved before recruiting participants with asthma to participate in their normal setting.

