### Outcome Measures

The primary measure is the number of participants who have obtained, or have updated, their written asthma action plan with a GP within the 12 months of the study. The secondary outcomes concern actual use rate of the written asthma action plan, number of unplanned visit to healthcare for asthma, usage of *Healthy.me*, asthma symptoms, and competing demands on health and asthma. Please see Table 1 below.

**Table 1 table1:** Summary of outcome measures.

Outcome measures		Measurement time points & methods		Time	
			Baseline	Monthly	Completion

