**Secondary outcomes**					
	Number of participants reported using their written asthma action plan, obtained, or updated during the study	Post-study survey	X		X
	Rate of planned (non-urgent) visits to a healthcare professional (eg, GP) for routine asthma management	Post-study survey			X
	Rate of unplanned visits to a GP, emergency department, caused by worsening asthma	Post-study survey			X
	Website usage patterns (number and timing of hits, duration of access, uptake of specific functions) of *Healthy.me*	*Healthy.me* system logs			X
	Technology acceptance of *Healthy.me*	Measured via the “Scales for Perceived Usefulness and Perceived Ease of Use” [30]			X
	Asthma control	Measured via “Asthma Control Questionnaire” [31]		X	
	Asthma exacerbations	Measured via the “Asthma Exacerbation Questionnaire” [32]		X	
	Number of days lost from work or school	Measured via an additional question after the “Asthma Control Questionnaire” [31]		X	
	Competing demands on health and asthma	Lists of life priorities and top health issues, monthly made by participants.		X	
					
					
					

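### Unplanned asthma visits are declared as a number or rate, but the only between-arm test stated in the article is on having had any such visit, so fewer repeat visits would not show

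*Protocol article*

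**What the plan says.** Three places in the protocol article declare the outcome:

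- Abstract, Results: "rate of planned and unplanned visits to healthcare providers for asthma issues".
- Outcome Measures, running text: "number of unplanned visit to healthcare for asthma".
- Table 1, secondary outcomes: "Rate of unplanned visits to a GP, emergency department, caused by worsening asthma", taken from the post-study survey.

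One place states how it is compared between arms. Secondary and Ancillary Analysis plans to examine "Differences in proportions of participants between different groups" by chi-square "for each of the following activities experienced at least once during the study". The first activity listed is having "visited a GP (or a healthcare professional) for an unplanned asthma visit".

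The same paragraph also plans a t-test or non-parametric comparison, for these quantities: "Differences in average number of days of absence per participant and differences in score distributions from questionnaires". Visits are not among them. Cost effectiveness of health service use is to be considered only if available and feasible, and is not a test of visit numbers.

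**The concern.** The variable declared and the variable tested are not the same. A number or rate of visits counts every visit. The any-visit indicator stops at the first. A participant with five unplanned visits and one with a single visit enter the chi-square table in the same cell.

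The trial hypothesizes better asthma control and fewer exacerbations. Part of such a benefit could be fewer repeat visits among people who still have at least one, and the stated test cannot detect that part. Leaving two versions of the outcome in print also leaves room to choose between them once the data are in.

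**Working it through.** **1. Is there a figure of the plan's own to reproduce?** Not for this outcome. The article gives no visit rate, dispersion or expected effect. The Sample Size section powers only the primary outcome, so its 300 participants serve here only to fix the number per arm.

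**2. Does the any-visit proportion determine the rate?** No. Suppose 40% of an arm have at least one visit (assumed). Write m for the mean number of visits and φ for the dispersion.

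- Poisson: m = −ln(0.6) = 0.51
- Negative binomial, φ = 1: m = 1/0.6 − 1 = 0.67
- Negative binomial, φ = 2: m = (1/0.36 − 1)/2 = 0.89

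The same proportion is compatible with means from 0.51 to 0.89, so a result on the proportion does not give a result on the rate.

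**3. How much power is at stake?**

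Inputs:
- n = 112 per arm, from 150 per arm and about 25% dropout (Sample Size): 150 × 0.75 = 112.5
- two-sided 5% level (Analysis Plan)
- assumed: negative binomial counts, φ = 1, rate ratio 0.67, control mean μ0 from 0.3 to 2.0, and μ1 = 0.67 μ0

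Formulas:
- Proportion with any visit: p = 1 − (1 + φμ)^(−1/φ), which for φ = 1 is μ/(1 + μ)
- Power, any-visit test: Φ{[(p0 − p1) − 1.96 √(2p̄(1 − p̄)/n)] / √([p0(1 − p0) + p1(1 − p1)]/n)}
- Power, count comparison: SE = √[(1/μ0 + 1/μ1 + 2φ)/n]; power = Φ(|ln 0.67|/SE − 1.96), with |ln 0.67| = 0.4005

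Lowest case, μ0 = 0.3, μ1 = 0.201:
- p0 = 0.3/1.3 = 0.231 and p1 = 0.201/1.201 = 0.167, giving 22% power
- SE = √[(3.333 + 4.975 + 2)/112] = 0.303; Φ(1.320 − 1.96) = 26%

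Highest case, μ0 = 2.0, μ1 = 1.34:
- p0 = 0.667 and p1 = 0.573, giving 30% power
- SE = √[(0.500 + 0.746 + 2)/112] = 0.170; Φ(2.353 − 1.96) = 65%

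| Control mean | Any visit, control v intervention | Power, any-visit test | Power, count comparison |
|---|---|---|---|
| 0.3 | 23% v 17% | 22% | 26% |
| 0.5 | 33% v 25% | 27% | 36% |
| 1.2 | 55% v 45% | 32% | 56% |
| 2.0 | 67% v 57% | 30% | 65% |

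A wider grid (rate ratio 0.7, control mean 0.5 to 2, φ from 0 to 2) gives 16% to 56% for the any-visit test and 25% to 93% for the count comparison. The count comparison is higher in every scenario tried.

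**The case against.** **The word rate may mean a proportion.** The article does use it that way: the hypotheses and the Sample Size section speak of rates when they mean the share of participants who obtain or hold a plan. On that usage, the Abstract and Table 1 could describe exactly what the chi-square compares. This stands in part. It does not remove the mismatch, because the Outcome Measures text names a number of visits, and Table 1 says number of participants in the rows where people are being counted.

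**A reader might infer that the declared outcome is never tested, or that the trial cannot report whether visits fell.** The documents do not support that. The article states one test and does not rule out analysing or reporting counts, and a statistical analysis plan that is not shown may add a count comparison. The point holds only for what this article states.

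**A reader might infer that the any-visit test is biased by unequal follow-up.** This is also not supported. The 9 to 12 months under Intervention Group and Exposure is time with access to the system, while Table 2 puts the post-trial survey at 12 months. The arms run concurrently under blocked 1:1 allocation, so staggered entry should balance. An offset for time observed is a refinement where follow-up differs, not the correction of a bias.

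**The binary choice has merit.** Table 1 takes visits from one self-completed post-study survey, so a count would rely on recall over up to 12 months. Having had any visit is plausibly less sensitive to miscounting and to a few frequent attenders. That is a good reason to keep the binary result, but not to let it stand in for a declared number.

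**The gain in power may be small.** Any adult with doctor-diagnosed asthma is eligible and intermittent asthma is a stratum, so low visit rates are plausible. At a mean of 0.3 the difference is four points and both tests are weak. The calculation also takes the negative binomial model as true, which favours the count comparison.

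**Conclusion.** The point holds as a mismatch in the printed text: a secondary outcome declared as a number or rate of unplanned visits has, in this article, only an any-visit test between arms. That conclusion does not rest on the power figures. The cost in power rests wholly on assumed visit means, dispersion and effect. With 112 per arm, dispersion 1 and a rate ratio of 0.67, it runs from about 4 percentage points (mean 0.3) to about 35 (mean 2.0). The chi-square is a valid test of what it tests, and the primary outcome is untouched. It should be changed, but it does not threaten the trial's main conclusion.

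**What to change.** In Secondary and Ancillary Analysis, compare the number of unplanned asthma visits per participant between arms with a count model, for example negative binomial regression, with log time observed as an offset where follow-up differs. Report the rate ratio with its 95% confidence interval. Keep the proportion with at least one visit as a supportive analysis.

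State one definition of the outcome in the Abstract, the Outcome Measures text, Table 1 and the analysis section. It should include the settings counted, since Table 1 names the emergency department and the analysis section names a GP or other healthcare professional. Redefining the outcome everywhere as the proportion with any visit would also remove the inconsistency, but would leave repeat visits outside the test.

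The cost is a change of wording, made before the allocation is revealed to the analysts. The survey must ask for a count, which the outcome as declared already implies, and that count carries recall error. Sample size and primary analysis do not change.
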